## Introduction

### Background

Stress urinary incontinence (SUI) is the most prevalent type of urinary incontinence (UI) accounting for half of women suffering from UI [1,2]. SUI is defined as the complaint of involuntary urine leakage on effort or physical exertion (eg, sports activities) or during sneezing or coughing [3]. Pregnancy and childbirth are regarded as the major predisposing factors of SUI [4]. About 40% of women experience SUI during pregnancy [5], and the prevalence of SUI after delivery is over one-fifth of women [6]. Other types include urgency UI, which is characterized by involuntary urine leakage with a strong desire to urinate, and mixed urinary incontinence, which is the combination of SUI and urgency UI [7]. UI negatively affects women’s activities of daily life, mental well-being, and quality of life [8-10].

Pelvic floor muscle training (PFMT) is the first-line therapy for SUI, and the National Institute for Health and Care Excellence recommends women perform PFMT, especially during pregnancy [11]. Despite the availability of this effective therapeutic option for SUI, less than 30% of women seek help from health care professionals [12,13]. The reasons for not seeking treatment are multifaceted, such as embarrassment, stigma, insufficient knowledge, and perception of SUI among pregnant women [14]. Besides, a shortage of obstetric health care professionals and time restrictions during appointments also impede the delivery of perinatal incontinence care [15]. Given the unoptimistic condition, effective strategies are urgently needed to overcome these barriers. With the rapidly evolving development of information and communication technologies, mobile health (mHealth) may be a novel and promising strategy to improve perinatal SUI care [16].

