### Eligibility of Participants

#### Inclusion Criteria

Pregnant women will be eligible if they are at least 18 years of age, have a singleton pregnancy according to ultrasonographic evaluation, are at 24-28 gestational weeks, have access to a mobile phone and the internet, and have SUI symptoms with ≥1 leakage episodes over the past 4 weeks (SUI symptoms are assessed by asking the question “When does urine leak?”). The question is an unscored item in the International Consultation on Incontinence Questionnaire-Urinary Incontinence Short Form (ICIQ-UI-SF), which has good reliability and validity [39]. SUI is defined as involuntary urine leakage on effort or physical exertion (eg, sports activities) or during sneezing or coughing [3]).

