### Data Management and Analysis

#### Quantitative Data

To avoid bias due to unnecessary face-to-face contact, data for pregnant women in both the intervention group and control group are collected electronically, using app-based and internet-based methods, respectively. After the data are exported from the app’s background management system and questionnaire website, data will be entered directly in a special database for the UIW app and saved in the database by researchers on a password-protected computer. Each participant is identified by a unique study ID assigned by the independent researcher assistant at the time of recruitment. And the “log” connecting the participants with the study IDs is held by the independent research assistant.

SPSS (version 25.0; IBM Corp, Armonk, NY) will be used for all quantitative data analysis. Descriptive statistics will be used to show continuous variables as mean (SD) and categorical variables as frequency and percentage. The baseline data will be compared between the intervention and control groups as well as between participants completing the follow-up of this study and those who drop out, with the independent sample *t* test for continuous variables and the chi-square test or Fisher exact test for categorical variables. The effects of the intervention within each group will be assessed with a paired *t* test for the severity of SUI, quality of life, and self-efficacy with PFMT and a McNemar chi-square test for risk factors. To compare the effects of the intervention between groups for the repeated measures, including severity of SUI, quality of life, and self-efficacy with PFMT, a linear mixed model will be used, which allows for missing data [57]. The model will include subjects as random effects and time, intervention, and the interaction between intervention and time as fixed effects. Pelvic floor muscle strength will be compared between groups using an independent sample *t* test. For the risk factors and PFMT adherence, chi-square tests will used to compare the differences between groups. *P* values <.05 will be considered statistically significant.

Participants with missing data will also be included in the analysis following the principle of intention-to-treat analysis. Missing data at follow-up will be replaced with the corresponding values at baseline.

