#### Sample Size Calculation

The sample size calculation was based on the primary outcome of the SUI symptom score, which is used to estimate the effect size in the power analysis [58]. A previous mobile app–based study performed among primiparas women showed a moderate effect size (0.344) [25]. G*Power [59] was used to estimate the sample size. A minimum sample size of 268 pregnant women is required for this study to achieve a power of 0.80 at a 2-sided significance level of .05. A 20% attrition rate is estimated based on previous studies involving mHealth interventions [60]. The total sample size was increased to 336, with 168 in each group.

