There are several potential limitations. One limitation may be that the sEMG will be only assessed at 42 days after delivery. Considering that an sEMG is conducted via a probe placed into the vagina, we will not assess sEMG during pregnancy due to the potential risk. Participants will seldomly return to the hospital after the reexamination at 42 days after delivery, and it is difficult to reach the participants. In view of feasibility and acceptability, the sEMG assessments will not also be conducted at 3 months and 6 months after delivery. Another limitation may lie in the requirements of having a mobile phone and access to the internet. It may lead to a more tech-savvy population who are more familiar and comfortable with mobile phone use and limit the generalizability to the whole population of pregnant women, although the rates of internet use and mobile phone ownership are relatively high. Finally, though the process evaluation is important to interpret the trial findings, it aims to provide transparency of the implementation of the intervention [64]. It only provides a possible explanation about the results rather than a full explanation.

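### Filling missing follow-up scores with baseline values leaves the chosen mixed model no missing data to handle, and biases the app effect by an amount that depends on dropout in each arm

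*Protocol article*

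**What the plan says.** All the relevant rules stand in the protocol article, under Data Management and Analysis, Quantitative Data.

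- For SUI severity (the primary outcome), quality of life and self-efficacy, "a linear mixed model will be used, which allows for missing data".
- On its terms: "The model will include subjects as random effects and time, intervention, and the interaction between intervention and time as fixed effects".
- On the analysis population: "Participants with missing data will also be included in the analysis following the principle of intention-to-treat analysis".
- The next sentence gives the replacement rule: "Missing data at follow-up will be replaced with the corresponding values at baseline". It exempts no visit, outcome or test, and it is not called a sensitivity analysis.

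On timing, Inclusion Criteria admits women who "are at 24-28 gestational weeks" and who already have SUI, so every baseline score is a pregnancy score from a woman who leaks. T1 follows the two-month intervention. T2, T3 and T4 fall 42 days, 3 months and 6 months after delivery.

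The Background puts SUI at about 40% of women in pregnancy and says that "the prevalence of SUI after delivery is over one-fifth of women". Sample Size Calculation states: "A 20% attrition rate is estimated based on previous studies involving mHealth interventions".

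**The concern.** The two missing-data statements conflict. A likelihood-based mixed model handles gaps by using whatever scores a woman does have. If every gap is first filled from baseline, that property is never used, and single imputed values enter with the same weight and certainty as measured ones.

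The rule also fixes what a dropout contributes: exactly zero change. That dilutes any real benefit. After delivery there is a second problem. A woman lost before T4 is scored as leaking at six months postpartum just as she did in mid-pregnancy, while women who stay are scored on what they report. If more women are lost from one arm, whatever improvement is common to both arms turns into a difference between them. The primary estimate, and in some cases its type I error rate, is at stake.

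**Working it through.** **Planned sample size.** For d = 0.344, two-sided 0.05 and power 0.80, the exact noncentral-t calculation gives 134 per arm, or 268 in total (power 0.801). Dividing by 1 − 0.20 gives 134/0.8 = 167.5, so 168 per arm and 336 in total. The stated figures reproduce; the sample size is not in error.

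**Inputs.** From the article: effect δ = 0.344 SD, 20% attrition, 168 per arm, 1:1 allocation. Assumed, because the article does not give them:
- SD 1 and correlation 0.5 between visits.
- Dropout that depends only on arm, with dropouts missing all follow-up.
- A shared improvement D from baseline to the visit concerned, ranged from 0 to 1 SD.
- Dropout fractions by arm, m_app and m_control.

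**Expected contrast.** Completers improve by D + δ with the app and by D in control. Filled-in women improve by 0. The mean changes are therefore (1 − m_app)(D + δ) and (1 − m_control)D, and their difference is

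(1 − m_app)·δ + (m_control − m_app)·D.

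With baseline present and all gaps filled, the model's intervention-by-time contrast equals this difference in mean change.

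**Estimates for true δ = 0.344.**

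| Dropout app / control | D | Calculation | Estimate |
|---|---|---|---|
| 20% / 20% | any | 0.80 × 0.344 | 0.275 |
| 25% / 15% | 0.5 | 0.258 − 0.05 | 0.208 |
| 25% / 15% | 1 | 0.258 − 0.10 | 0.158 |
| 15% / 25% | 0.5 | 0.292 + 0.05 | 0.342 |
| 15% / 25% | 1 | 0.292 + 0.10 | 0.392 |

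**No true effect (δ = 0).** Only (m_control − m_app)·D remains. It is 0 with equal dropout, and ±0.05 (D = 0.5) or ±0.10 (D = 1) with a 10-point imbalance. Simulating the random-intercept model's T4 minus T0 contrast gives false rejection of about 8% at D = 0.5 and 17% to 18% at D = 1. With equal dropout it stays near 5%.

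**Power with equal 20% dropout and δ = 0.344.** The same simulation gives about 0.80, 0.78 and 0.75 at D = 0, 0.5 and 1. Power falls little because the standard error shrinks along with the estimate. At D = 0, completers' change has variance 2(1 − 0.5) = 1 and dropouts' change has variance 0, so the pooled variance is about 0.8. The ratio of estimate to standard error is 0.275/√(0.8 × 2/168) = 2.82. Using only 134 completers per arm it is 0.344/√(2/134) = 2.82. Power is kept at the price of an estimate 20% too small, with invented zero changes counted as data. With 25% app and 15% control dropout, power drops to about 0.55 (D = 0.5) or 0.33 (D = 1).

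**The case against.** Several points on the other side stand.

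- **Which tests the rule covers.** It might be meant only for the paired t and chi-square tests. The text does not say so, and if that was the intention the sentence still needs correcting.
- **Power.** A reader might infer that 0.80 is lost in any case. It is not, when dropout is equal. A figure of 0.65 to 0.71 can be obtained, but it belongs to a t test on follow-up scores, which is not the analysis planned for this outcome.
- **Direction.** A reader might infer that the rule always works against the app. With more control dropout it can restore the true value by accident (0.342) or exceed it (0.392).
- **Size of recovery.** A reader might infer large natural improvement from the two prevalences. They are population figures with separate citations, and the postpartum one is a lower bound. They suggest lower leakage after delivery, but give no within-woman change in ICIQ-UI-SF points.
- **Imbalance.** The article gives one overall attrition figure and predicts no difference between arms. It does collect data by different routes in the two arms (app and website), so equality cannot be presumed either.
- **Visit.** The section on secondary outcomes refers to the primary outcome score at the end of the intervention. T1 comes about two months after 24 to 28 weeks and is generally still in pregnancy, so the postpartum argument does not reach it. Dilution does.
- **sEMG.** The article says "One limitation may be that the sEMG will be only assessed at 42 days after delivery". A reader might call the rule unworkable for this outcome. With no baseline value the wording simply does not reach it, and its missing-data handling is a detail an article may leave to the analysis plan.

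**Conclusion.** The concern holds in this form. The article states a rule, without limit, that cancels the missing-data property for which its own model was chosen, and that rule governs the primary comparison.

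Dilution of a true effect by the app arm's dropout fraction follows at any visit when dropout is equal: 0.344 becomes about 0.275 SD at 20%. For T2 to T4, the added bias from unequal dropout runs in either direction and equals the dropout difference times D. Its size rests on an assumed D and an assumed imbalance, so the values above are illustrations, not predictions. Baseline replacement would be correct only if women who leave truly stay at their baseline score, which is hardest to defend after delivery. It cannot be excused as reliably conservative.

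**What to change.** Remove baseline replacement from the primary analysis. State that the linear mixed model already specified is fitted to all observed ICIQ-UI-SF, IIQ-7 and BPMSES scores of all randomized women, with no prior imputation. Women with partial follow-up stay in the analysis, so the intention-to-treat aim is kept.

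Keep baseline replacement, or another departure from missing at random such as multiple imputation under a stated alternative assumption, only as a labelled sensitivity analysis. Report dropout by arm and visit beside it.

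The cost is a change of wording: no new data are needed, and the model is the one already planned. The downside is that the primary result then relies on missing at random, which is itself an assumption in an unblinded app trial. The sensitivity analysis is there to test it.

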#### Sample Size Calculation

The sample size calculation was based on the primary outcome of the SUI symptom score, which is used to estimate the effect size in the power analysis [58]. A previous mobile app–based study performed among primiparas women showed a moderate effect size (0.344) [25]. G*Power [59] was used to estimate the sample size. A minimum sample size of 268 pregnant women is required for this study to achieve a power of 0.80 at a 2-sided significance level of .05. A 20% attrition rate is estimated based on previous studies involving mHealth interventions [60]. The total sample size was increased to 336, with 168 in each group.

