Risk factors for SUI among pregnant women will be assessed using a self-designed questionnaire, investigating weight, condition of constipation, active and passive smoking, and consumption of liquids containing caffeine.

For the dimension of Adoption, the pregnant women’s PFMT adherence and activity in the 2 groups, usage results and patterns of use of the UIW app for the intervention group, other possible apps and websites used by the control group, and facilitators and barriers to adoption of the app will be explored through quantitative and qualitative methods. PFMT adherence and activity as well as usage results and patterns will be evaluated using quantitative methods through the log data of the background management system for the intervention group; a self-administered, electronic PFMT diary; and an electronic questionnaire (Multimedia Appendix 5). For the qualitative interviews, we will adopt a purposive sampling strategy to select women from the 2 groups based on the primary outcome of the SUI symptom score at the end of the intervention. Pregnant women will be selected at a ratio of 1:1 in the higher and lower scores until achieving data saturation such that no new themes emerge during data analysis. The interviews will be performed by a researcher ([name]) via telephone or face-to-face. The interviewer is a female nurse with a master’s degree in nursing science and formal training in qualitative studies. A semistructured interview guide was developed by the research team and covers the topics of user experiences, preferences, and expectations (Multimedia Appendix 5). Data collection, management, and analysis will be carried out concurrently, which makes it possible to adapt and refine the interview guide [56]. All interviews were audiotaped after gaining permission from the participants.

For the dimension of Implementation, the fidelity of the intervention and usual care provided will be evaluated (Multimedia Appendix 5).

For the dimension of Maintenance, the measures used to assess “Effectiveness,” “Adoption,” and “Implementation” will be repeatedly assessed in the follow-up period at the T2, T3, and T4 time points.

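### The stated 80% power belongs to a single two-group comparison, and the protocol never says which term or visit of the planned mixed model that comparison is

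*Protocol article*

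**What the plan says.** The Primary Outcome section defines the outcome by instrument, the ICIQ-UI-SF total score, without a visit or contrast. It is collected at baseline (T0), at the end of the intervention (T1) and at three visits after delivery (T2 to T4).

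The Sample Size Calculation section takes an effect size of 0.344 from an earlier app trial, sets alpha at 0.05 (two-sided), and states: "A minimum sample size of 268 pregnant women is required for this study to achieve a power of 0.80". Allowing for 20% dropout, it then concludes: "The total sample size was increased to 336, with 168 in each group". It names the software but no test, visit, number of measurements or within-woman correlation.

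The Quantitative Data section compares the arms on SUI severity with a linear mixed model: "The model will include subjects as random effects and time, intervention, and the interaction between intervention and time as fixed effects". The only decision rule is that P "values <.05 will be considered statistically significant".

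Under the Maintenance dimension, in the Secondary Outcomes section, the effectiveness measures "will be repeatedly assessed in the follow-up period at the T2, T3, and T4 time points".

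**The concern.** A power statement is informative only if it refers to the test that will decide the trial. Here the sample size was set for one comparison between two groups. The analysis section offers at least three candidates for the deciding test: the intervention effect across visits, the interaction, or a between-arm difference at a particular visit. These answer different questions. T1 falls two months after entry at 24 to 28 weeks of gestation, so normally before delivery, whereas T2 to T4 are all after it.

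Two things are at stake. A reader cannot tell what chance the trial has of detecting the assumed effect on its primary outcome. And while the deciding test is open, it could be chosen after the results are known, in which case the 5% level would not describe the primary claim.

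**Working it through.** **Inputs from the protocol:** two-sided alpha 0.05, power 0.80, effect size 0.344 (read as a mean difference in SD units), 1:1 allocation, 20% attrition, five visits of which four are post-baseline, and a random subject effect.

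**Assumptions (not in the protocol):** within-woman correlation ρ of 0.3, 0.5 or 0.7, equal for all pairs of visits as a random-intercept model implies; SD of 1 at each visit; and the course of the effect over time.

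**1. The protocol's own figure.** For a two-sample t test, the noncentrality is d·√(n/2) with 2n − 2 degrees of freedom. At n = 134 it is 0.344 × √67 = 2.82 and power is 80.1%. At n = 133 power is 79.8%. The minimum is therefore 134 per arm, or 268. Attrition: 134/0.8 = 167.5, rounded up to 168 per arm, or 336. Both figures reproduce. A one-sided test would need 210 and does not fit. The document does not say "t test"; that is inferred from the exact match.

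**2. Interaction test (4 df), 134 per arm.** The noncentrality is λ = (n/2)·Σ(δₖ − δ̄)²/(1 − ρ), where δₖ is the between-arm difference at visit k.
- Sustained effect, δ = (0, 0.344, 0.344, 0.344, 0.344): mean 0.2752, sum of squares 0.2752² + 4 × 0.0688² = 0.0947, so λ = 67 × 0.0947/(1 − ρ).
- Fading effect (100/75/50/25% at T1 to T4): mean 0.172, sum of squares 2 × 0.172² + 2 × 0.086² = 0.0740, so λ = 67 × 0.0740/(1 − ρ).

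| Effect course | ρ = 0.3 | ρ = 0.5 | ρ = 0.7 |
|---|---|---|---|
| Sustained: λ | 9.1 | 12.7 | 21.1 |
| Sustained: power | 67% | 83% | 97% |
| Fading: λ | 7.1 | 9.9 | 16.5 |
| Fading: power | 55% | 71% | 92% |

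These use the noncentral chi-square. The noncentral F agrees to within one percentage point (54% instead of 55% in the lowest cell).

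**3. Intervention effect averaged over all five visits, 134 per arm.** The standard error is √[(2/n)(ρ + (1 − ρ)/5)] = 0.081, 0.095 and 0.107 at ρ = 0.3, 0.5 and 0.7. Baseline contributes a true difference of zero to the average.

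| Effect course | Averaged effect | ρ = 0.3 | ρ = 0.5 | ρ = 0.7 |
|---|---|---|---|---|
| Sustained T1 to T4 | 4 × 0.344/5 = 0.275 | 92% | 83% | 73% |
| T1 only | 0.344/5 = 0.069 | 14% | 11% | 10% |

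**4. A T1 contrast, 134 per arm.** The between-arm difference at T1 with complete data has the precision of step 1, hence 80%. The between-arm difference in change from T0 to T1 has variance 4(1 − ρ)/n, giving 66%, 80% and 95%. The wording of the contrast therefore matters.

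**5. Error rate.** One named contrast, or one global interaction test, keeps 5%. If any of the four post-baseline between-arm contrasts at .05 could count as the primary result, simulation of four equally correlated two-sided tests gives a false-positive chance of 17.4%, 15.6% and 13.0% at correlation 0.3, 0.5 and 0.7.

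**The case against.** **The document leans to T1.** It places T2 to T4 under Maintenance, lists the primary outcome under Effectiveness, and refers to the primary outcome at the end of the intervention when describing how interviewees are chosen. On that reading the sizing fits a T1 comparison and only a sentence is missing. This largely stands, and it is why T1 is the natural choice. But the interview wording selects participants rather than defining a test, and the Background and Discussion frame the aim as improvement during and after pregnancy. T1 is implied, not set.

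**Underpowering is not shown.** A reader might infer that the trial is too small. The documents do not support that: correlation and effect course are not given, and the results fall on both sides of 80%. Sizing on a two-group comparison and then fitting a mixed model is also common practice.

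**Nor is a lost 5% level.** A reader might infer that success on any visit or term counts. The Quantitative Data section does not plan four separate visit tests of this outcome with any hit sufficing. The .05 rule reads as a general threshold, and the 13% to 17% is conditional on a use of the model that the text leaves open but does not state.

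**The detail may sit elsewhere.** The list of measures (Multimedia Appendix 5) and any SAP are not shown and may name the visit. Even so, the article makes a power claim and fixes a model, and the two do not connect as written.

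**Conclusion.** The point holds as a mismatch between the power statement and the planned analysis. The arithmetic behind 268 and 336 is correct. The 0.80 describes one two-group comparison with 134 observed women per arm; it is not a property of the mixed model until a term or visit is named. Depending on that choice, and under the stated assumptions about correlation and effect course, the same 268 women give anything from about 10% (averaged effect, benefit at T1 only) to 97% (interaction, correlation 0.7, sustained effect). The direction is not established. The 5% level is unsecured rather than lost.

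**What to change.** State one primary contrast: the between-arm difference in ICIQ-UI-SF at T1, estimated from the mixed model, two-sided .05. This agrees with placing T2 to T4 under Maintenance and with the sizing. Make T2, T3 and T4 secondary, reported as estimates with confidence intervals or tested in the fixed order T1, T2, T3, T4.

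In the sample size section, say that the 0.80 refers to a two-group comparison at T1 with 134 observed women per arm. It should not be claimed for an analysis in which missing follow-up values are replaced by baseline values, as the Quantitative Data section also provides. For illustration, assume 20% are missing at T1, the replaced values show no between-arm difference and the SD is unchanged: the effect becomes 0.8 × 0.344 = 0.275 and power at 168 per arm is about 71%.

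The cost is wording only; sample size, visits and data collection stay as they are. The downside is that a benefit seen only after delivery could not be called the primary result.
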